### Patient level: clinical effectiveness outcome and implementation assessment

The primary outcome variables to assess clinical effectiveness will be the clinic level proportion of patients with diabetes who: (a) receive any CRC screening and (b) complete a colonoscopy at 12 months from baseline. An exploratory analysis will assess clinic-level CRC screening completion by glucose control (controlled vs. uncontrolled, i.e., HbA1c > 9 at 12 months). Patient level data is collected in aggregate and will include no identified personal health information.

Patient acceptability will be assessed through the assessment of patient rates of opting-out and non-adherence of CRC screening. This rate will be based on the proportion of CRC screening among patients with diabetes compared to overall eligible patient population (without diabetes) in each clinic.

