### Evaluation of the effectiveness and implementation of SURE: CRC4D

The effectiveness and implementation of SURE: CRC4D will be evaluated using a mixed method learning evaluation strategy, where ongoing data collection and analysis are used to refine implementation to optimize adoption of CRC screening for patients with diabetes [52, 53]. This evaluation is designed to address two research questions: (1) are the adapted implementation strategies clinically effective in increasing CRC screening rates for patients with diabetes; and, (2) are the implementation strategies feasible and acceptable to implementers (e.g., clinicians and staff) and patients in FQHCs? This evaluation builds an evidence base about the effectiveness of the implementation strategies in a real-world context and allows for the collection of data that can be used to refine the implementation toolkit for a larger scale, definitive cluster randomized controlled trial. Guided by EPIS, contextual factors were selected based on suggestions from clinical stakeholders, community partners, and previous literature suggesting they may influence implementation success [54–56] (see Table 4). The following assessments and measures will be collected to evaluate the trial:

**Table 4 Tab4:** Study measures

	Baseline & 12-month post implementation

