**Effectiveness: Clinic Level Patient Outcomes***	
Demographics	QUANT
Glycemic Control (HgbA1C < 9)	QUANT
Any CRC screening/patients eligible	QUANT
Colonoscopy completion/patients eligible	QUANT
CRC rate by glycemic control	QUANT

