### Quantitative analysis

Descriptive statistics will be used to summarize patient and clinic characteristics. We will declare our intervention a success if at least 25% of those unscreened are screened at 12-month follow-up in this difficult to reach population. We will declare the optimization of screening a success if 15% of those unscreened are screened with a colonoscopy or flexible sigmoidoscopy at 12-months. Overall improvement metrics are comparable to improvements in previous CRC screening implementation studies in FQHCs [65, 66]. At baseline, we will calculate average screening rates and their confidence intervals across all practice sites in intent to treat analyses and at 12-months we will assess screening rates and their confidence intervals for all sites. The confidence intervals will be compared to 25%. We will compare differences in CRC screening by glucose control, sex, and race/ethnicity.

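### The exploratory comparison of screening by glucose control groups patients by HbA1c at 12 months, the end of the window in which screening is counted, and can show a gap that starting control did not cause

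*Protocol article*

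**What the plan says.** In the protocol article, the section on patient-level clinical effectiveness outcomes sets the comparison up as exploratory: "An exploratory analysis will assess clinic-level CRC screening completion by glucose control (controlled vs. uncontrolled". It defines the groups as "controlled vs. uncontrolled, i.e., HbA1c > 9 at 12 months". The time point sits inside the parenthesis that defines the groups, so it dates the HbA1c. The same paragraph gives the primary outcomes as the clinic-level proportions of patients who receive any screening and who "complete a colonoscopy at 12 months from baseline".

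Table 4 lists "CRC rate by glycemic control" as an effectiveness measure under the column "Baseline & 12-month post implementation". It also lists glycemic control itself, "Glycemic Control (HgbA1C < 9", under that column. The table note says these measures are drawn from the electronic health record in aggregate at both times.

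The Quantitative analysis section returns to the comparison without dating the HbA1c: "We will compare differences in CRC screening by glucose control, sex, and race/ethnicity".

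**The concern.** Sex and race/ethnicity, the other two factors in the planned comparison, are not altered by a year of follow-up. HbA1c is. A patient who attends, takes part in diabetes care and answers outreach may be more likely both to complete screening and to finish the year with a lower HbA1c. The 12-month group is then partly a result of the behaviour that also produces the outcome. A difference between the groups cannot be separated from that shared cause, so it does not show that uptake depends on glycemic control.

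A smaller defect sits beside this. Table 4 defines control as below 9, and the text defines lack of control as above 9. A value of exactly 9 belongs to neither group, and six clinics could assign it differently.

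**Working it through.** **The plan's own sample size.** The Power calculations section takes 50 patients with diabetes per clinic and expects 40% to be up to date. 50 × (1 − 0.40) = 30 per clinic, and 6 × 30 = 180. This reproduces the stated 30. The article gives no figure for the glycemic-control comparison.

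**Timing of each item**

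| Item | When measured | Where |
|---|---|---|
| Screening completed | Baseline to 12 months | Patient-level outcomes section |
| HbA1c used for grouping | 12 months | Patient-level outcomes section |
| Glycemic control as a listed measure | Baseline and 12 months | Table 4 |
| HbA1c for the comparison by glucose control | Not dated | Quantitative analysis |

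The grouping value is taken at the end of the outcome window, although a baseline value is planned.

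**Size of the possible artefact.** Two inputs are anchored in the article. One third are taken as uncontrolled at baseline (Background: more than a third of patients with diabetes in these health centers). Overall screening is 25% (the success threshold). Everything else is assumed: half the patients are engaged, independently of baseline control, and screening depends on engagement only. Grouping by baseline HbA1c therefore gives a difference of exactly 0.

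Let s be the probability of screening, r the probability that an uncontrolled patient becomes controlled, and w the probability that a controlled patient worsens. In each engagement half:

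- uncontrolled at 12 months: u = 0.5 × [(1/3)(1 − r) + (2/3)w]
- controlled at 12 months: c = 0.5 − u
- screening rate in a 12-month group = Σ(share × s) / Σ(share), summed over the two halves

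Example, row (c) below:

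- Engaged: u = 0.5 × [(1/3)(0.50) + (2/3)(0.05)] = 0.10, c = 0.40.
- Not engaged: u = 0.5 × [(1/3)(0.90) + (2/3)(0.15)] = 0.20, c = 0.30.
- Uncontrolled: (0.10 × 0.35 + 0.20 × 0.15) / 0.30 = 21.7%.
- Controlled: (0.40 × 0.35 + 0.30 × 0.15) / 0.70 = 26.4%.

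| Row | s, engaged / not | r, engaged / not | w, engaged / not | Controlled | Uncontrolled | Gap (points) |
|---|---|---|---|---|---|---|
| null | 25% / 25% | 50% / 10% | 5% / 15% | 25.0% | 25.0% | 0 |
| (a) | 30% / 20% | 40% / 20% | 5% / 10% | 25.3% | 24.1% | 1.2 |
| (b) | 35% / 15% | 40% / 20% | 5% / 10% | 25.7% | 23.2% | 2.5 |
| (c) | 35% / 15% | 50% / 10% | 5% / 15% | 26.4% | 21.7% | 4.8 |
| (d) | 40% / 10% | 50% / 10% | 5% / 15% | 27.1% | 20.0% | 7.1 |

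**Cross-check with a simpler mechanism.** Per 100 patients, let 35 be uncontrolled at baseline and screen 25% in both groups. That gives 8.75 screened and 26.25 unscreened uncontrolled, and 16.25 and 48.75 controlled. Assume 30% of screened and 10% of unscreened uncontrolled patients reach control, and no controlled patient worsens.

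- Uncontrolled at 12 months: 6.125 / (6.125 + 23.625) = 20.6%.
- Controlled at 12 months: 18.875 / (18.875 + 51.375) = 26.9%.
- Gap: 6.3 points. With 20% versus 10% reaching control it is 3.1 points, and with 15% versus 10% about 1.5.

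**Scale.** With 180 patients split 60 and 120 at 25% screened, ignoring clustering, SE = √[0.25 × 0.75 × (1/60 + 1/120)] = 6.8 points. The 80% interval half-width is 1.28 × 6.8 ≈ 8.8 points.

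**The case against.** The strongest reply is that the article poses no predictive question. Table 4 can be read as a repeated cross-section: the screening rate by current control, tabulated at each extraction. On that reading a 12-month HbA1c at the 12-month extraction is coherent, and the exploratory label fits. This reading is possible, and such a table is legitimate as description. It does not rescue the comparison as evidence that uptake depends on glycemic control, and setting glucose control beside sex and race/ethnicity invites that interpretation.

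The size is also fairly contested. The rates of HbA1c change are assumed, a 6.3-point gap lies near the top of the range, and almost all of the range is below one standard error. The one-third figure describes health-center patients with diabetes in general, not those overdue for screening. All of this stands and limits the severity.

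Four stronger readings are tempting but unsupported:

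- A reader might infer that HbA1c is taken after the outcome window. The article puts both at 12 months.
- A reader might infer that patients without a 12-month HbA1c are dropped. The article does not say so, and missing-data handling is commonly left to a fuller document. That such patients would be mostly unscreened is conjecture.
- A reader might infer that the result would misdirect the toolkit. The toolkit is for patients with type II diabetes as a whole, and nothing says this comparison will steer it.
- A reader might infer that the change is wording only. Separate aggregate totals at baseline and 12 months cannot be linked afterwards.

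**Conclusion.** The point holds as a low-severity fault in an exploratory analysis. The stated grouping uses a post-implementation value that can share a cause with the outcome, although a baseline value is planned. The spurious gap is about 1 to 7 points under the assumed rates and zero if engagement does not affect screening. Its direction here, with controlled patients appearing to screen more, follows from assuming that engagement helps both screening and HbA1c. At 180 patients the artefact would be hard to distinguish from sampling error, but a larger sample would not remove it. The primary outcomes and the 25% and 15% success criteria do not use HbA1c and are unaffected. The gap between below 9 and above 9 is a wording inconsistency to be reconciled.

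**What to change.** 1. For patients on each clinic's registry as eligible at baseline, define glycemic control by the baseline HbA1c already planned in Table 4, with a stated look-back period.
2. Have each clinic return 12-month counts of any screening and of colonoscopy, cross-tabulated by baseline HbA1c category, with a separate category for no HbA1c on record.
3. Use one boundary rule in Table 4 and in the text, so that a value of exactly 9 falls in one group.
4. Give the same time point in the Quantitative analysis section.
5. If a table by 12-month HbA1c is kept, label it a concurrent description and draw no conclusion from it about whether control affects uptake.

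The cost is one linked cross-tabulation per clinic, six in all. It must be written into the data request before extraction, because aggregate returns may not allow it to be recovered later. Sample size, primary outcomes and success criteria do not change.

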## Background

Patients with diabetes mellitus have an estimated 27% elevated lifetime risk of developing colorectal cancer (CRC), and are disproportionately from priority health disparities populations (e.g., low-income, Non-Hispanic Black and Hispanic) [1, 2]. Nationally, guideline concordant receipt of CRC screening for patients with diabetes is not significantly different for women with diabetes (57% vs. patients without diabetes 58%) and is significantly higher among men with diabetes (63% vs. patients with diabetes 58%) [3]. CRC screening for patients with diabetes, who do not have other indications of high risk (e.g., family history of CRC, polyp removal during colonoscopy, personal history of CRC, inflammatory bowel disease) are advised to follow the average risk screening recommendations [4]. Federally qualified health centers (FQHCs) primarily serve as primary care for priority health disparities populations and struggle to sustainably implement CRC screening programs for average-risk patients which includes patients with diabetes. CRC screening uptake in FQHCs populations has been consistently lower (44.1%) than the national average for average risk, age-eligible adults (67.3%) [5].

Persons receiving diabetes care in FQHCs have elevated health risks overall and higher rates of poverty and low-income status than the general population [6]. Ten percent of FQHC patients have a diabetes diagnosis and more than a third within this group have uncontrolled diabetes (HbA1c > 9%). Failure to implement preventive CRC screenings translates to an average of 6.5 years of lost life for patients subsequently diagnosed with CRC [7]. Moreover, this contributes to greater burden for patients with diabetes who are diagnosed with CRC who suffer greater morbidity, all-cause mortality, and cancer-specific mortality compared to CRC patients [8–10]. Therefore, efforts to prioritize CRC screening for patients with diabetes are needed in primary care safety-net settings.

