### Methods

#### Study participants and setting

This single arm trial will be conducted in six FQHC clinical sites in New Jersey. Eligibility criteria for the FQHC clinics include: (1) provide care to at least 450 patients aged 50–74 years; (2) 10% of patient population previously diagnosed with diabetes; (3) located in New Jersey; and, 3) clinical and administrative leadership willing to engage in the intervention and research requirements (interviews, data validation, process evaluation). Implementation outcomes will be assessed using mixed methods guided by the EPIS constructs (see Table 2). The methods of this study have been reported using Standard Protocol Items: Recommendation for Interventional Trials (SPIRIT) guidelines (Supplemental file 1).

During the implementation a clinic-based registry of patients eligible for CRC screening will be developed for each clinic at baseline and updated at six and 12 months post-baseline. Patient eligibility criteria will include: (1) patients not up-to-date or due for CRC screening [4]. based on electronic health record (EHR) documentation (e.g. FOBT/FIT test in last year, flexible sigmoidoscopy within 4 years, or colonoscopy within 9 years), (2) previous diagnosis of type II diabetes, (3) age-eligible for CRC screening (45–74 years of age) and (4) ) FIT/FOBT that has been ordered for more than 6 months that has not been completed or a sigmoidoscopy or colonoscopy referral that has not been completed for 12 or more months. Patients are excluded if they have EHR documentation medical conditions not concordant with standard CRC screening intervals (e.g. prior CRC diagnosis, inflammatory bowel disease, renal failure, etc.) [4].

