### Implementation strategies

The goal of SURE: CRC4D is to enable FQHC clinics to adopt strategies to optimize the use of evidence based colorectal cancer screenings (See Table 1) uptake for patients with type II diabetes. To accomplish this, multi-level, multi-component implementation strategies (see Table 3) will be utilized. The core components of this implementation effort includes the identification and engagement of 2–3 clinic change champions, who will participate in two virtual learning collaborative events [38–41] and lead the change effort in the clinic aided by bi-weekly virtual practice facilitator support [38, 42–49]. The SURE: CRC4D toolkit will include guidance on pulling data to develop and implement quality monitoring systems to provide regular audit/feedback to the clinic, patient educational materials in English and Spanish and dissemination materials for clinical meetings to orient other clinic members to the change process being implemented to optimize CRC screening for patients with diabetes [50, 51]. Clinic champions will tailor toolkit resources as clinics may have different electronic medical records, type and composition of staff, clinical workflows, and standing clinical team meetings.

**Table 3 Tab3:** Timeline for implementation activities & assessment

Single Group	Year in months											
**Implementation Activities**	1	2	3	4	5	6	7	8	9	10	11	12
Identify clinical champions	x											
Learning collaborative	x		x									
Virtual Practice facilitation	x	x	x									
Patient Education Materials	x											
Clinical Meeting Materials	x	x										
Quality Monitoring System	x	x	x	x								

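### Patient acceptability is scored against patients without diabetes in the same intervention clinics, whose own screening the programme can shift in either direction

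*Protocol article*

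**What the plan says.** In the protocol article, the section Patient level: clinical effectiveness outcome and implementation assessment first names the events of interest: "Patient acceptability will be assessed through the assessment of patient rates of opting-out and non-adherence of CRC screening". It then says how the rate is obtained: from the "proportion of CRC screening among patients with diabetes compared to overall eligible patient population (without diabetes) in each clinic". It does not say whether the comparison is a difference, a ratio or a change from baseline, or which direction is favourable.

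Table 4 lists patient acceptability as a quantitative implementation outcome. Its note schedules the data in aggregate from the electronic health record at baseline and 12 months.

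On design, Study participants and setting states: "This single arm trial will be conducted in six FQHC clinical sites in New Jersey". On delivery, Implementation strategies has champions who "lead the change effort in the clinic aided by bi-weekly virtual practice facilitator support", a toolkit with guidance on pulling data to "develop and implement quality monitoring systems to provide regular audit/feedback to the clinic", and meeting materials to "orient other clinic members to the change process being implemented to optimize CRC screening for patients with diabetes".

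**The concern.** A benchmark for acceptability should not respond to the programme being judged. Here the benchmark group attends the same six clinics and is served by staff whom the strategies are meant to change.

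Two opposite effects are plausible:

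- **Spillover.** Champions, audit and feedback, and meetings may raise screening for everyone. Equal gains in both groups would then look like no gain in acceptability.
- **Diversion.** The planning work set out to give priority to patients with diabetes (Methods and design). The Background calls these clinics under-resourced and says that they "struggle to sustainably implement CRC screening programs for average-risk patients which includes patients with diabetes". If effort moves away from other patients, their screening falls and the contrast improves although no patient with diabetes has behaved differently.

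At stake is the reading of one implementation outcome. Patient acceptability belongs to the second trial objective and the second research question, and Table 4 gives it this one quantitative measure. The planned interviews on acceptability are with staff and clinicians, so they would not directly correct a misleading patient-level figure. A possible unwanted effect of a targeted programme, displacement of other eligible patients, could be counted in its favour.

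**Working it through.** **1. The plan's own figure.** Power calculations assumes 50 patients with diabetes per clinic, 40% of them up to date: 50 x (1 - 0.40) = 30 per clinic, and 6 x 30 = 180 in all. This reproduces the stated target. The article gives no figure for the acceptability comparison.

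**2. The structure of the measure.** Let D be the screening proportion with diabetes and N the proportion without, in the same clinic. As a difference, the measure is D - N, and its change over time is (change in D) - (change in N). If D does not change, the measure moves by exactly minus the change in N. A ratio D/N likewise rises when N falls. This holds whichever group starts higher.

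**3. Can N move because of the programme?** With a single arm, no clinic is untreated. Champions lead change in the clinic, feedback goes to the clinic, and other clinic members are oriented to the change. The content is aimed at patients with diabetes, but nothing in the article keeps the strategies away from other patients or says how a change in their screening would be handled. So N can move; the article does not show that it will.

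**4. Illustration.** D is held at 25%, the success threshold in Quantitative analysis, used only for scale. The article gives no value for N, so its unaffected level (10% or 20%) and its shift are assumptions.

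| Unaffected N | Shift in N (points) | N | D - N (points) | D/N |
|---|---|---|---|---|
| 10% | -5 (diversion) | 5% | +20 | 5.0 |
| 10% | 0 | 10% | +15 | 2.5 |
| 10% | +5 (spillover) | 15% | +10 | 1.67 |
| 10% | +10 (spillover) | 20% | +5 | 1.25 |
| 10% | +15 (spillover) | 25% | 0 | 1.0 |
| 20% | -5 (diversion) | 15% | +10 | 1.67 |
| 20% | 0 | 20% | +5 | 1.25 |
| 20% | +5 (spillover) | 25% | 0 | 1.0 |

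The opposite ordering behaves the same way. With D at 25% and N falling from 40% to 30% (assumed), D - N goes from -15 to -5, an apparent improvement of 10 points. If both groups rise by 10 points, D - N is 35 - 50 = -15, unchanged.

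**5. Scale against the planned precision.** The 80% confidence interval half-width for 25% of 180, without clustering, is 1.2816 x sqrt(0.25 x 0.75 / 180) = 0.041, or 4.1 points. With an assumed intracluster correlation of 0.05, the design effect is 1 + 29 x 0.05 = 2.45, and the half-width is 4.1 x sqrt(2.45) = 6.5 points. A 5-point shift in N exceeds the first figure but not the second; shifts of 10 or 15 points exceed both. These half-widths are for the rate with diabetes alone, not for the contrast.

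**The case against.** The strongest reply is that exposure of the comparator is inferred. The goal, the registry and the meeting materials are all directed at patients with type II diabetes, and no section says that other patients receive anything. Displacement is likewise conjecture: saying that clinics struggle with average-risk screening does not say that helping one group harms another. This stands. The supportable statement is that the comparator can be affected, not that it is.

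Second, the article gives no scoring rule, and the rates used above are assumed. This also stands: the table shows how the measure behaves, not how large the distortion will be. But any comparison of D with N has this property, so the missing rule does not remove the problem.

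Third, rates for both groups are needed at baseline and 12 months, so a fall among patients without diabetes could be noticed. That is true if both rates are shown separately, but the article does not say that they will be.

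Fourth, in a single-arm study, patients seen in the same clinics over the same period carry some information on background trend. That is a fair reason to keep their rates as context, though not to call the contrast acceptability.

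A reader might also infer that a decision on national roll-out rests on this measure. The article does not support that. The success rules in Quantitative analysis are the 25% and 15% thresholds among unscreened patients, neither of which uses the comparator. The Discussion describes further testing of scalability and sustainability, and the evaluation section points to a definitive cluster randomized trial.

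**Conclusion.** The point holds in a limited form. The between-group screening contrast cannot be read as patient acceptability, because it can change when only the comparator changes, and the clinic-level design gives plausible routes for that in both directions. This rests on the stated definition, the single arm and delivery through clinics and staff.

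The size and net direction cannot be determined from the article. Under the assumed comparator level of 10%, the difference ranges from 0 to +20 points with screening in patients with diabetes fixed at 25%. That range is an illustration, not an estimate.

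The stronger reading, that patients without diabetes are known to be exposed or will be displaced, is not supported. The primary outcomes and both success rules are unaffected. The consequence is confined to one implementation outcome, which is nevertheless the only patient-acceptability measure listed.

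**What to change.** In the section that defines patient acceptability:

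1. Base acceptability on the events already named there, opt-out and non-completion, counted among eligible patients with diabetes, and not on the contrast with patients without diabetes. Report opt-out on its own line: non-completion among all eligible patients is close to the complement of the primary outcome of any screening and adds little alone.
2. Report the screening rate in each group separately, per clinic, at baseline and 12 months.
3. Name the change among patients without diabetes as a descriptive balancing outcome. Read a rise as possible spillover or background trend, and a fall as possible displacement. Keep the between-group contrast only as context for background trend.

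**Cost.** This is mainly rewording and reporting. The rates without diabetes are already needed for the current definition and, by the Table 4 note, fall due at baseline and 12 months. Opt-outs must be identifiable in the record, but the current text already presupposes that by naming them. The downsides are one more reported outcome, which may be unfavourable, and a reduced role for the contrast.
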